## Abstract

Preclinical studies have shown that volatile anesthetics may have beneficial effects on injured lungs, and pilot clinical data support improved arterial oxygenation, attenuated inflammation, and decreased lung epithelial injury in patients with acute respiratory distress syndrome (ARDS) receiving inhaled sevoflurane compared to intravenous midazolam. Whether sevoflurane is effective in improving clinical outcomes among patients with ARDS is unknown, and the benefits and risks of inhaled sedation in ARDS require further evaluation. Here, we describe the SESAR (Sevoflurane for Sedation in ARDS) trial designed to address this question. SESAR is a two-arm, investigator-initiated, multicenter, prospective, randomized, stratified, parallel-group clinical trial with blinded outcome assessment designed to test the efficacy of sedation with sevoflurane compared to intravenous propofol in patients with moderate to severe ARDS. The primary outcome is the number of days alive and off the ventilator at 28 days, considering death as a competing event, and the key secondary outcome is 90 day survival. The planned enrollment is 700 adult participants at 37 French academic and non-academic centers. Safety and long-term outcomes will be evaluated, and biomarker measurements will help better understand mechanisms of action. The trial is funded by the French Ministry of Health, the European Society of Anaesthesiology, and Sedana Medical.

## 1. Introduction

Volatile anesthetics such as isoflurane or sevoflurane have long been used to provide general anesthesia in the operating room; however, inhaled sedation is emerging as an option to provide intensive care unit (ICU) sedation and a phase III multicenter randomized controlled trial found that isoflurane is non-inferior to propofol in maintaining targeted sedation levels in critically ill adult patients [1,2,3,4,5]. Preclinical studies have shown that inhaled sevoflurane improves gas exchange [6,7,8], reduces alveolar edema [8], and attenuates pulmonary and systemic inflammation [9,10] in experimental models of acute respiratory distress syndrome (ARDS).

In addition to their potential effects on mechanisms relevant to ARDS [11], findings from clinical studies in critically ill patients suggest that volatile anesthetics may provide superior awakening and extubation times in comparison with intravenous sedatives such as propofol and benzodiazepines [12,13]. In a previous pilot randomized controlled trial of patients with moderate to severe ARDS, inhaled sevoflurane, compared to intravenous midazolam, improved oxygenation and decreased inflammation and lung epithelial injury, as assessed by plasma and an alveolar soluble receptor for advanced glycation end-products (sRAGE), interleukin (IL)-1β, IL-6, IL-8, and tumor necrosis factor (TNF)-α [14]. In this study and others [15,16,17], sevoflurane inhalation through dedicated devices was well tolerated, with no major adverse effects [18]. This pilot trial was underpowered to evaluate mortality or other major clinical outcomes. Given the number of ICU patients with ARDS receiving sedation and the overall burden of ARDS on healthcare, especially since the coronavirus disease 2019 (COVID-19) pandemic, improving clinical outcomes through sedative choice would have important implications globally.

The phase III multicenter clinical trial, SESAR (Sevoflurane for Sedation in ARDS), was designed to examine the efficacy and safety of a strategy of inhaled sevoflurane sedation compared with a strategy of current intravenous sedation practice using propofol in patients with ARDS.

## 2. Materials and Methods

The complete trial protocol, as currently approved, is provided in Supplementary Material File S1.

### 2.1. Objectives

We hypothesize that a strategy of inhaled sedation with sevoflurane may be more effective than current intravenous sedation practice in improving clinical outcomes in ARDS. We investigate our hypotheses through the following objectives:To examine the efficacy of inhaled sevoflurane versus intravenous propofol in improving a composite outcome of mortality and time off the ventilator at 28 days in ARDS.To evaluate the safety of inhaled sevoflurane in ARDS (clinical adverse events), to describe its effects on the duration of mechanical ventilation, organ dysfunction, the use of rescue procedures, ICU-acquired delirium, major clinical and long-term outcomes, and healthcare-related costs during ICU and hospital stay.To investigate the physiological and biological mechanisms of protection by inhaled sevoflurane in ARDS, if any, and their potential roles in heterogeneity of treatment effects.

### 2.2. Trial Design

The SESAR trial is an investigator-initiated, two-arm, parallel-group, randomized controlled trial with a blinded outcome assessment. The primary endpoint is the number of days alive and off the ventilator at 28 days (ventilator-free days through day 28, VFD28), thereby considering death as a competing event. The planned enrollment is 700 adult participants at 37 French clinical sites. The trial protocol was approved by an ethics committee (*Comité de Protection des Personnes Ile-de-France* 2, approval number 18.09.21.60651-RIPH1) and the French Medicine Agency (*Agence Nationale de Sécurité du Médicament et des Produits de Santé*, approval number MEDMSANAT-2019-09-00248). The trial has been designed in accordance with the Standard Protocol Items: Recommendations for Interventional Trials guidelines (Supplementary Material File S2).

### 2.3. Eligibility Criteria and Exclusions

Adult patients under invasive mechanical ventilation with ARDS [19] and a PaO_2_/FiO_2_ <150 mmHg under a positive end-expiratory pressure (PEEP) ≥8 cmH_2_O are enrolled, such as in the *ARDS et Curarisation Systematique* and *Reevaluation of Systemic Early Neuromuscular Blockade* trials [20,21]. A SpO_2_/FiO_2_ that is equivalent to a PaO_2_/FiO_2_ <150 mmHg can be used when an arterial blood gas is not available [22]. Exclusion criteria include known pregnancy, suspected or proven intracranial hypertension, persistent bronchopleural fistula despite chest tube drainage, long QT syndrome at risk of arrhythmic events, a medical history of malignant hyperthermia, liver disease attributed to previous exposure to volatile anesthetics, hypersensitivity or anaphylactic reaction to sevoflurane, propofol or cisatracurium, current treatment with sevoflurane or extracorporeal membrane oxygenation (ECMO) at enrollment, enrollment in another interventional trial with direct impact on sedation or mechanical ventilation, or if their tidal volume of 6 mL/kg predicted body weight (PBW) is below 200 mL (as recommended by the manufacturer of the device used to deliver inhaled sevoflurane in the trial). As oxygenation may improve during the 24 h enrollment window, an exclusion criterion is a PaO_2_/FiO_2_ >200 mmHg (if available) after meeting inclusion criteria and before randomization. Full eligibility criteria are listed in Table 1.

Due to eligibility criteria, patients will not be able to provide informed consent at enrollment and the study protocol provides for a waiver of informed consent from the patient. In case the patient’s legally authorized representative cannot be reached during the 24 h time window for enrollment, the investigator can include the patient using an emergent consent procedure and deferred informed consent will be obtained as soon as possible from the participants. The CONSORT diagram of the SESAR trial is provided in Figure 1.

### 2.4. Randomization

All patients were randomized online (CSOnline, Clinsight) by local investigators within 24 h of meeting inclusion criteria on a 1:1 ratio for the two study arms. The randomization sequence was generated by minimization and stratified by the study center, the degree of ARDS severity (PaO_2_/FiO_2_ < 100 mmHg), the suspicion or presence of COVID-19, and the presence of shock (defined as intravenous infusion of vasoactive drugs) at enrollment.

### 2.5. Treatment Arms, Administration, and Standardization of Care

#### 2.5.1. Interventions

Study interventions are summarized in Figure 2.

#### 2.5.2. Study Arms: Intervention—Inhaled Sedation with Sevoflurane

Sevoflurane is vaporized via the miniaturized Anesthesia Conserving Device (Sedaconda ACD-S, Sedana Medical, Danderyd, Sweden), which is placed between the endotracheal tube and the Y-piece of the ventilator breathing circuit. The residual expired gas is scavenged following the manufacturer’s instructions using an active carbon filter (Flurabsorb, Sedana Medical, Danderyd, Sweden) [1]. As recommended by the manufacturer, Sedaconda ACD is replaced every 24 h and removed from the breathing circuit as soon as inhaled sedation is interrupted and for spontaneous breathing trials. Sevoflurane administration is interrupted, and the Sedaconda ACD-S removed from the breathing circuit, if severe acidemia (pH < 7.15) is present, in the absence of metabolic acidosis and despite tidal volume and/or respiratory rate increase, or if malignant hyperthermia or a bronchopleural fistula that is persistent despite drainage (to limit room exposure) develops. In these situations, sedation is switched to a strategy of intravenous propofol.

#### 2.5.3. Study Arms: Control—Intravenous Sedation with Propofol

Propofol is administered via continuous intravenous infusion, as routinely used in participating ICUs. Propofol is interrupted if propofol-related infusion syndrome develops; in these cases, management and the choice of sedative agent(s) is as per the treating clinicians.

#### 2.5.4. Common Strategies for Both Groups

Upon randomization, deep sedation is protocolized (Richmond Agitation-Sedation Scale (RASS) −4 to −5) and combined with the neuromuscular blockade (continuous infusion of cisatracurium besylate for a maximum of 48 h) in both groups. The neuromuscular blockade is continued until PaO_2_/FiO_2_ exceeds 150 mmHg for 4 h with FiO_2_ < 0.6 [21,23,24]; then, light sedation is targeted (RASS 0 to −1), with prompt sedation interruption whenever possible. In both arms, patients receive the allocated sedation strategy from randomization until sedation can be interrupted or until day 7, whichever occurs first. When sedation is required again within 7 days after randomization, the sedative agent to use is based on the randomization arm; after day 7, decisions on sedation are as per the treating clinicians. If the bispectral index (BIS^®^, Aspect Medical Systems Inc., Norwood, MA, USA) is available, the level of sedation under the neuromuscular blockade can be titrated and monitored using the BIS^®^, with a targeted value of 40–50 [14]. Pain management is conducted as per clinical teams, within a strategy of analgesia-first sedation, including frequent pain assessment with the behavioral pain scale (BPS); opioids agents, if needed, are those routinely used in participating centers.

Lung-protective ventilation is used in both arms [25]. Using volume-controlled ventilation, tidal volume is set at 6 mL/kg (+/− 2 mL/kg) of PBW [26], and PEEP is kept as high as possible without increasing the inspiratory plateau pressure above 28–30 cmH_2_O [27]. We allow deviation from the high PEEP strategy if there is clinical concern that the use of high PEEP may be worsening oxygenation, if hypotension and/or high inspiratory plateau pressure (>30 cmH_2_O) are present despite further tidal volume reduction and/or respiratory rate increase, if a study participant develops a pneumothorax, is at high risk for barotrauma, or as per the treating clinicians. Instrumental dead space of the respiratory circuit is reduced to the minimum in both arms. Whenever possible, we recommend sites to wait at least 12 h before proning for more than 12 h/day, one or multiple times as per the treating clinicians [23,26]. Fluid management during shock is unrestricted; however, in patients not in shock, a conservative fluid approach is recommended (Supplementary Material File S3) [28]. If PaO_2_ ≥ 55 mmHg or SpO_2_ ≥ 88% with FiO_2_ of 1 cannot be maintained, clinicians may employ rescue procedures, chosen according to the practice at the clinical site, such as recruitment maneuvers, nitric oxide, ECMO, or neuromuscular blockade use after 48 h from randomization. Evidence-based recommendations for weaning from mechanical ventilation will be applied in both groups (Supplementary Material File S4). All participating centers have existing protocols and order sets for routine sedation management, glucose control, septic shock resuscitation, deep venous thrombosis prophylaxis, and other aspects of background care.

#### 2.5.5. Standardization and Adherence

Although all participating critical care professionals are certified and allowed to manage ICU sedation, their previous use and expertise level of inhaled sevoflurane may vary [4]. An educational program is conducted prior to patient recruitment to ensure that all participating centers have sufficient training to ensure patient safety and reach study goals through online-based theoretical presentations and online and on-site practical training. The study sponsor (CHU Clermont-Ferrand) safeguards data quality monitoring via web-based data collection, monthly query reports, site visits, and structured data collection training. A steering committee supervises the trial.

### 2.6. Patient Timeline, Assessments, and Measures

Patients are assessed as described in the Time-Events schedule (Supplementary Material File S5). Long-term outcomes are assessed on days 90 and 365 (Supplementary Material File S6). It is not technically possible to mask the assigned sedation strategy to the treating clinicians, due to the nature of the intervention requiring specific equipment. However, patients are followed up by members of the research staff from each site who are unaware of the group allocation. Study data are collected into the electronic case report form (CSOnline, Clinsight, Paris, France) by trained research staff blinded to the allocation group.

### 2.7. Trial Outcome Measures

The trial outcome measures are summarized in Table 2.

#### 2.7.1. Primary Outcome

The primary outcome is the number of days alive and off invasive mechanical ventilation at 28 days (ventilator-free days at 28 days, VFD28), considering death as a competing event. VFD28 are defined as the number of days from the time of initiating unassisted breathing to day 28 after randomization, assuming survival for at least two consecutive calendar days after initiating unassisted breathing and continued unassisted breathing to day 28. A period of assisted breathing lasting less than 24 h and for the purpose of a surgical procedure does not count against the VFD calculation, and VFDs are zero if a patient dies prior to day 28.

#### 2.7.2. Key Secondary Outcomes

The key secondary outcome is 90 day survival.

#### 2.7.3. Secondary Outcomes

Other secondary outcomes are all-location, all-cause mortality at 7, 14, and 28 days, and all-cause hospital 28 day mortality.

#### 2.7.4. Exploratory Outcomes

Exploratory outcomes are VFD7, VFD14, organ failure-free days through day 7 [evaluating Sepsis-related Organ Failure Assessment (SOFA) scores [29]], ICU-free and hospital-free days through day 28, respiratory physiological measures (oxygenation index, PaO_2_/FiO_2_, PaCO_2_, arterial pH, PEEP, inspiratory plateau pressure, static compliance of the respiratory system, and ventilatory ratio, as defined as [minute ventilation (mL/min) × arterial PaCO_2_ (mmHg)]/[predicted body weight *×* 100 *×* 37.5] [30]), use of rescue procedures for refractory hypoxemia through day 28, ICU-acquired delirium through day 7 or ICU discharge or death (whichever comes first), long-term outcomes at 3 and 12 months (disability, health-related quality of life, self-rated health, pain-interference, post-traumatic stress-like symptoms, cognitive function, subsequent return to work, healthcare use, and location of residence), and healthcare-related costs during ICU stay and stay (secondary analysis). Instruments for ICU-acquired delirium and long-term outcome assessment are detailed in Supplementary Material File S6.

#### 2.7.5. Exploratory Biological Outcomes

Exploratory biological outcomes are changes over time in plasma biomarkers including IL-8, soluble tumor necrosis factor-receptor 1, bicarbonate (hyperinflammatory ARDS phenotype [31]), IL-6 (ventilator-induced lung injury [25,32]), angiopoietin 2 (endothelial activation [33,34]), and sRAGE (alveolar epithelial injury [35,36]), in urine biomarkers including tissue inhibitor of metalloproteinase 2 and insulin-like growth factor binding protein 7 (acute kidney injury [37]), in plasma total fluoride and hexafluoroisopropanol (sevoflurane metabolism), in total protein within undiluted pulmonary edema fluid (alveolar fluid clearance [36]), in biomarker measurements in the fluid from heat moisture exchanger filters (control group) or Sedaconda ACD-S devices (intervention group) [38,39] and in the bronchoalveolar lavage fluid, and genetic analyses (Table 2).

#### 2.7.6. Safety Outcomes

Safety outcomes are hemodynamic (mean arterial pressure, dose of infused norepinephrine or other vasopressor, serum lactate level) and renal function (KDIGO criteria [40]) measures through day 7 and development of severe hypercapnic acidosis with arterial pH < 7.15 (Sedaconda ACD-S device), supraventricular tachycardia or new onset atrial fibrillation during the ICU stay, malignant hyperthermia (sevoflurane), propofol-related infusion syndrome (propofol), and bronchopleural fistula that is persistent despite drainage (to limit room exposure to sevoflurane) through day 7.

### 2.8. Laboratory Evaluations

In addition to laboratory studies obtained as per routine clinical care, plasma and urine samples will be collected, when available, at study entry and on days 1, 2, 4, 6, and 14 or ICU discharge (whichever occurs first) to investigate the biological effects of inhaled sevoflurane in ARDS. We will also collect whole blood samples at study entry and on day 2 for RNA and DNA studies. In selected centers, undiluted pulmonary edema fluid samples will be collected at study entry and 24 h later in 50 patients from each group; bronchoalveolar lavage fluid will be sampled in 25 intubated patients within 48 h from study entry and between day 4 and day 6; fluid from heat moisture exchanger filters and Sedaconda ACD-S devices will be collected at 24 h in 30 patients from each group.

#### 2.8.1. Safety Data

Serious and unexpected adverse events, such as unexpected deaths (i.e., not related to the progression of the primary disease or to limitation of care), severe hypercapnic acidosis that may be related to the intervention (arterial pH < 7.15, in the absence of metabolic acidosis and despite further tidal volume and/or respiratory rate increase) or the development of malignant hyperthermia, propofol-related infusion syndrome or bronchopleural fistula persistent despite drainage, will be reported to the sponsor by the investigators.

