#### 2.8.2. Data and Safety Monitoring

Interim safety reports are performed by the sponsor to the independent data monitoring and safety committee (DMSC), consisting of two clinician-scientists and a methodologist-biostatistician, each time 40 patients are enrolled [14], including blinded variables on randomization-stratification variables (site, severe ARDS, COVID-19, and shock at enrollment), serious and unexpected adverse events, and the rates and causes of death at day 28. An interim analysis is preplanned on data from 350 patients (175 by group), with symmetric group sequential flexible stopping boundaries [41]. Recommendations for continuing, pausing, or stopping the study will be made by the DMSC to the steering committee for superiority of either active or control, or potential safety reasons. The observation of differences in serious adverse events between the two groups allows unblinding of the group allocations if deemed necessary by the DMSC.

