Exploratory outcomes	Ventilator-free days through day 14 (VFD14) Ventilator-free days through day 7 (VFD7) Organ failure-free days through day 7 ** ICU-free days through day 28 Hospital-free days through day 28 Physiological measures to include: o Changes in oxygenation index, PaO_2_/FiO_2_, PaCO_2_, and arterial pH from day 1 to day 7 (defined as continuous time-dependent variables) o Changes in the level of PEEP (and static auto-PEEP in patients under controlled ventilation), inspiratory plateau pressure and static compliance of the respiratory system, and in ventilatory ratio^#^ from day 1 to day 7 (defined as a continuous time-dependent variable) Use of rescue procedures for refractory hypoxemia through day 28: nitric oxide, epoprostenol sodium, high frequency ventilation, ECMO, and neuromuscular blockade use after 48 h from randomization. ICU-acquired delirium: CAM-ICU assessed daily from study entry to study day 7, death or ICU discharge, whichever comes first. Long-term outcome assessments at 3 and 12 months: o Disability: Katz Activities of Daily Living o Health-Related Quality of Life: Short Form-36 o Pain-interference: 1 standard item o Post-traumatic Stress-like Symptoms: Post-Traumatic Stress Symptoms-14, Hospital Anxiety and Depression Scale o Cognitive function: Alzheimer’s Disease 8 o Subsequent return to work, hospital and ED use, and location of residence Healthcare-related costs during ICU stay and hospital stay
Exploratory biological outcomes	Change in plasma biomarkers of IL-8, sTNFr1, bicarbonates (hyperinflammatory ARDS phenotype), IL-6 (VILI), ANG-2 (endothelial activation), and sRAGE (alveolar epithelial injury) (defined as continuous time-dependent variables) ^§^ Change in urine biomarkers of TIMP-2 and IGFBP-7 (acute kidney injury) ^§^ Change in plasma total fluoride and hexafluoroisopropanol (sevoflurane metabolism) Genetic analysis: DNA and RNA at baseline and 48 h Change in total protein within undiluted pulmonary edema fluid at baseline and 24 h (alveolar fluid clearance) ^£^ Biomarker measurements in the fluid from the HME filter (control group) and Sedaconda ACD-S device (intervention group) at baseline and 24 h ^$^ Biomarker measurements in the BAL fluid within 48 h from study entry and between day 4 and day 6 ^€^

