Safety outcomes	Changes in hemodynamic measures (mean arterial pressure, dose of infused norepinephrine or other vasopressor, serum lactate level) and in KDIGO criteria for acute kidney injury from day 1 to day 7 (defined as continuous time-dependent variables) Supraventricular tachycardia or new onset atrial fibrillation through day 7 Severe hypercapnic acidosis with arterial arterial pH < 7.15 ^%^ through day 7 (Sedaconda ACD-S device) Development of malignant hyperthermia through day 7 (sevoflurane) Development of propofol-related infusion syndrome through day 7 (propofol) Development of pneumothorax or bronchopleural fistula persistent despite drainage, through day 7

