*Definition of abbreviations:* SESAR = sevoflurane for sedation in acute respiratory distress syndrome; VFD = ventilator-free days; ICU = intensive care unit; PEEP = positive end-expiratory pressure; ECMO = extracorporeal membrane oxygenation; CAM-ICU = confusion assessment method for the ICU; ED = emergency department; IL-8 = interleukin 8; sTNFR1 = soluble tumor necrosis factor receptor 1; IL-6 = interleukin 6; ANG-2 = angiopoietin 2; sRAGE = soluble receptor for advanced glycation end-products; TIMP-2 = tissue inhibitor of metalloproteinase 2; IGFBP-7 = insulin-like growth factor binding protein 7; DNA = deoxyribonucleic acid; RNA = ribonucleic acid; HME = heat moisture exchanger; BAL = bronchoalveolar lavage; KDIGO = kidney disease improving global outcomes. * Ventilator-free days through day 28 are defined as the number of days from the time of initiating unassisted breathing to day 28 after randomization, assuming survival for at least two consecutive calendar days after initiating unassisted breathing and continued unassisted breathing to day 28. If a patient returns to assisted breathing and subsequently achieves unassisted breathing to day 28, VFDs will be counted from the end of the last period of assisted breathing to day 28. A period of assisted breathing lasting less than 24 h and for the purpose of a surgical procedure will not count against the VFD calculation. If a patient was receiving assisted breathing at day 27 or dies prior to day 28, VFDs will be zero. Patients transferred to another hospital or other healthcare facility will be followed to day 28 to assess this endpoint. ** Organ failure is defined as present on any date when the most abnormal vital signs or clinically available lab value meets the definition of clinically significant organ failure according to SOFA scores. Patients will be followed for the development of organ failures to death, hospital discharge, or study day 7, whichever comes first. Each day a patient is alive and free of a given organ failure will be scored as a failure-free day. Any day that a patient is alive and free of all organ failures will represent days alive and free of all organ failure. # Ventilatory ratio = [minute ventilation (mL/min) × PaCO_2_ (mmHg)]/[predicted body weight × 100 × 37.5] ^§^ Plasma and urine samples will be collected from indwelling catheters (when available) at study entry and on days 1, 2, 4, 6, and 14 or ICU discharge (whichever occurs first). ^£^ In 50 patients from each group. ^$^ In 30 patients from each group. ^€^ In a total of 25 patients. ^%^ In the absence of metabolic acidosis and despite further tidal volume and/or respiratory rate increase, as described in the protocol.

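### Severe hypercapnic acidosis has three different definitions, and the one used for serious adverse event reporting may under-capture control-arm events in the counts that the DMSC reviews

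*Protocol article*

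**What the plan says.** The event appears in three places in the protocol article.

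- **Section 2.7.6 (Safety Outcomes)** lists "development of severe hypercapnic acidosis with arterial pH < 7.15 (Sedaconda ACD-S device"). The only criterion is the pH threshold.
- **Table 2 (Safety outcomes)** lists the same event through day 7, with a footnote: "In the absence of metabolic acidosis and despite further tidal volume and/or respiratory rate increase, as described in the protocol".
- **Section 2.8.1 (Safety Data)** covers what investigators report to the sponsor. The list opens with "Serious and unexpected adverse events, such as unexpected deaths" and goes on to "severe hypercapnic acidosis that may be related to the intervention", defined as "arterial pH < 7.15, in the absence of metabolic acidosis and despite further tidal volume and/or respiratory rate increase".

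Four other statements bear on how the event is captured and used.

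- Section 2.5.2 labels the sevoflurane arm as the intervention. It attaches the combination of pH < 7.15, no metabolic acidosis and failed ventilator changes to a rule for interrupting sevoflurane. Section 2.5.3 has no pH-triggered counterpart for propofol.
- Section 2.6 says that treating clinicians cannot be masked, while the research staff who enter the case report form data are blinded.
- Section 2.8.2 says that the DMSC receives reports each time 40 patients are enrolled. The named contents are the stratification variables, serious and unexpected adverse events, and the rates and causes of death at day 28. It adds: "The observation of differences in serious adverse events between the two groups allows unblinding of the group allocations", if the DMSC deems this necessary.
- Table 2 also lists, as exploratory outcomes without an arm limit, "Changes in oxygenation index, PaO_2_/FiO_2_, PaCO_2_, and arterial pH from day 1 to day 7".

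**The concern.** This is the harm that the article itself links to the delivery device, so its count should mean the same thing in both arms and in every table.

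First, the three texts do not identify the same patients. A patient with mixed acidosis below the pH threshold is an event under section 2.7.6 and a non-event under the Table 2 footnote.

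Second, two conditions in section 2.8.1 are unlikely to work evenly across arms. A propofol patient has no device, so an investigator who knows the allocation has less reason to see a low pH as possibly related to the intervention. The ventilator-change condition is written into a pH-triggered rule only for sevoflurane, so a control event may fail it because the step was never tried or recorded for that purpose.

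At stake is the interim view of safety. If control events are captured less completely, a between-arm difference in serious adverse events could partly reflect reporting, and the article allows unblinding on such a difference.

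**Working it through.** **Step 1. The three definitions side by side.**

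| Condition | 2.7.6 | Table 2 with footnote | 2.8.1 |
|---|---|---|---|
| Arterial pH < 7.15 | yes | yes | yes |
| No metabolic acidosis | not stated | yes | yes |
| Persists despite ventilator changes | not stated | yes | yes |
| May be related to the intervention | not stated | not stated | yes |

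**Step 2. A patient who separates them.** Use pH = 6.1 + log10[HCO3 / (0.03 × PaCO2)]. With bicarbonate 20 mmol/L and PaCO2 60 mmHg (illustrative values), pH = 6.1 + log10(20 / 1.8) = 7.146. This meets the pH criterion of section 2.7.6. Under Table 2 and section 2.8.1 it can be set aside as having a metabolic component.

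**Step 3. Unequal capture.** The article states no event rate or capture rate, so both are assumed. Take n = 350 per arm (section 2.8.4), the same true rate p in both arms, full capture on sevoflurane (p1 = p) and a fraction c on control (p2 = c·p). The chance of a two-sided p < 0.05 is about

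Φ[(p1 − p2 − 1.96·SE0) / SE1], where SE0 = √[p̄(1 − p̄)·2/n], SE1 = √[(p1(1 − p1) + p2(1 − p2))/n] and p̄ = (p1 + p2)/2.

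Worked case, p = 5% and c = 50%: p1 = 0.05, p2 = 0.025, p̄ = 0.0375, SE0 = 0.01436, SE1 = 0.01433. Then (0.025 − 1.96 × 0.01436) / 0.01433 = −0.22, and Φ(−0.22) = 0.41.

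| True rate in both arms | c = 75% | c = 50% | c = 25% |
|---|---|---|---|
| 3% | 9% | 27% | 59% |
| 5% | 13% | 41% | 82% |
| 10% | 22% | 71% | 99% |

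With equal capture the figure would be about 5%. These results are for full enrollment. Interim reports rest on fewer patients, and the article names no test for serious adverse events, so the table illustrates sensitivity to capture and is not an error rate of the trial.

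**Step 4. The metabolic-acidosis condition, if it removes the same share in each arm.** Take true rates of 10% and 5%, a risk ratio of 2. With 25% of events lost, the counted rates are 7.5% and 3.75%. The risk ratio is still 2, but the risk difference falls from 5 to 3.75 percentage points. By the same formula, power with 350 per arm falls from 71% to 58%, and to 41% if 50% of events are lost. The absolute rate and precision suffer, but the risk ratio is not biased by this alone.

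**The case against.** The strongest reply is that section 2.8.1 is only a channel for reports to the sponsor. Its list is illustrative, its wording is a possible relation, which is a low bar, and nothing in it bars a serious and unexpected control-arm event. Section 2.5.1 also uses the word interventions for both arms. The device name in brackets in section 2.7.6 and Table 2 parallels the drug names beside the other events. It names a suspected source and does not limit counting to one arm. The qualifiers mirror the interruption criterion in section 2.5.2, so outcome and device action line up. The full protocol and the analysis plan are not shown and may settle the capture rules.

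Most of this stands, and it rules out several stronger readings that a reader might infer:

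- **That control events are excluded by definition, or that the arms cannot be compared.** The Table 2 outcome has no relatedness condition or arm limit, the pH and PaCO2 outcomes run from day 1 to day 7, and blinded staff enter the case report form data.
- **That events in shock patients drop out.** Section 2.4 defines shock by vasoactive infusion, with no acid-base condition. Only acidosis with a metabolic component is set aside, under the same words in both arms.
- **That the metabolic condition biases the comparison by itself.** Step 4 shows that equal loss leaves the risk ratio unchanged.

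The reply does not remove the printed disagreement between the three texts. It also leaves the interim problem: the contents named in section 2.8.2 include serious and unexpected adverse events but neither the Table 2 acidosis outcome nor the blood gases. That list may not be complete, but as printed the more neutral data are not among what the DMSC is said to see.

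**Conclusion.** The point holds as a matter of inconsistent definition and possible unequal capture. The three texts must be reconciled whatever the supplementary files say, because they classify the same patient differently. The risk of bias is confined to the serious adverse event counts that reach the DMSC. It rests on two inferences: that investigators read the intervention as the sevoflurane arm, and that they consider relatedness less readily for propofol patients. Both are plausible from sections 2.5.2 and 2.6, but neither is demonstrated.

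On assumed true rates of 3% to 10%, the chance of a spurious nominal difference at full enrollment is 9% to 22% with 75% control capture and 27% to 71% with 50%. The documents supply neither rate. The final safety comparison is not lost, though the count and absolute risk depend on which definition is applied. This is a worthwhile, inexpensive correction and does not invalidate the safety evaluation.

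**What to change.** Use one definition in section 2.7.6, Table 2 and section 2.8.1, and drop the relatedness condition for this event. Derive it in both arms from recorded blood gases: arterial pH < 7.15 together with a PaCO2 cut-off fixed before any comparison by arm, regardless of judged cause, metabolic component or ventilator response. Show it by arm in the DMSC reports and the final safety table. Report events meeting the current qualifiers as a subset, so that the more device-specific signal stays visible.

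The cost is a wording change and one derived variable, since arterial pH and PaCO2 from day 1 to day 7 are already trial outcomes. The downside is a higher count that includes some acidosis not caused by the device. The cut-off governs how much: at PaCO2 50 mmHg, pH 7.15 corresponds to bicarbonate of 0.03 × 50 × 10^1.05 = 16.8 mmol/L, so a low cut-off would admit many events with a large metabolic component. The change concerns counting and reporting only and leaves the treatment-interruption rule as it is.
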